#### Blood Pressure Monitor

The BP monitor (Withings S.A., Issy les Moulineaux, France) is a smartphone-compatible, battery operated oscillometric BP cuff. The device allows the user to measure systolic BP, diastolic BP, and heart rate. The device is applied around the left or right upper arm (depending on the patient’s preference). Upon pushing the button on the cuff, a connection is made with the smartphone via Bluetooth. The inflation and deflation of the cuff is automated and can be initiated via the dedicated Withings Health Mate app (for iOS and Android) on the smartphone. The average duration of a measurement is approximately 20 seconds. After inflation and deflation, the systolic blood pressure (SBP), diastolic blood pressure (DBP), and heart rate are shown on the smartphone screen.

#### The Weight Scale

The weight scale (Withings S.A., Issy les Moulineaux, France) allows the patient to track weight, fat percentage, heart rate, and ambient CO_2_ parts per million. To measure all four parameters, the patient must stand on the weight scale. While standing on the weight scale, the patient must select their own account. The results are shown on a screen on the weight scale, and are automatically uploaded via the Internet to the Withings server.

#### Activity Tracker

The activity tracker (Pulse Ox, Withings S.A., Issy les Moulineaux, France) allows the patient to track the number of steps taken per day. The device is the size of a thumb and can be attached to the wrist or belt, and also allows the patient to track duration and quality of sleep. Steps are automatically tracked. The measurement results are sent via Bluetooth to a dedicated smartphone app, which is compatible with iOS and Android OS.

### Storage of the ECGs

Single lead ECGs, generated by the single lead ECG device, are stored in the cloud. The system offers patients the ability to connect their personal account with a physician’s account. The physician can then review the ECGs made by patients linked to their account, including the diagnosis given by the app’s algorithm and the symptoms reported by the patient. The automated diagnosis algorithm has a reported sensitivity of 97% and a specificity of 98% for the detection of atrial fibrillation [7]. ECGs that are classified by AliveCor as *possible atrial fibrillation* and *undetermined* will subsequently be checked by a project-dedicated health care professional in our department. A patient will be contacted if a previously undiagnosed arrhythmia is seen or if a patient repeatedly reports symptoms. A flowchart of the storage of the ECGs is shown in Figure 3. An example of a portable document format (PDF) ECG showing sinus rhythm generated by the ECG device is shown in Figure 4. An example of a PDF ECG showing atrial fibrillation generated by the ECG device is shown in Figure 5.

**Figure 3 figure3:**

Data integration of single lead electrocardiograms. Company A is the ECG manufacturer. ECG: electrocardiogram.

**Figure 4 figure4:**
[figure not shown]
A PDF generated by the ECG device, showing sinus rhythm.

**Figure 5 figure5:**
[figure not shown]
A PDF, generated by the ECG device, showing atrial fibrillation.

### Data Integration in Electronic Medical Records

The measurement results from the weight scale, BP monitor, and activity tracker will be stored on the manufacturer’s server (Withings S.A., Issy les Moulineaux, France). Data will be extracted from the Withings server and integrated in the department’s dedicated electronic medical record (EMR; EPD-Vision, Department of Cardiology, LUMC, The Netherlands). An automated algorithm searches for predefined irregularities in the data (Textbox 2). Data can subsequently be displayed in graphic format to facilitate trend analysis. A flowchart of the storage of BP, weight, and activity data is displayed in Figure 6. If bugs arise in this system, a software developer who works at the Department of Cardiology will fix the bug.

Warnings generated by the dedicated system.BP monitorIf a patient has not sent BP results for more than 7 consecutive daysIf the heart rate is >100 beats per minuteIf the SBP is >139If the DBP is > 89If the SBP is 10 mmHg higher than last measurementIf the DBP is 5 mmHg higher than last measurementIf the SBP is 10 mmHg higher than 7 measurements beforeIf the DBP is 5 mmHg higher than 7 measurements beforeIf the SBP is 10 mmHg lower than last measurementIf the DBP is 5 mmHg lower than last measurementIf the SBP is 10 mmHg lower than 7 measurements beforeIf the DBP is 5 mmHg lower than 7 measurements beforeWeight scaleIf a patient has not sent measurements for more than 7 consecutive daysIf the weight is more than 2 kg higher than last measurementIf the weight is more than 3 kg higher than 7 measurements beforeIf the weight is more than 2 kg lower than last measurementIf the weight is more than 3 kg lower than 7 measurements beforeActivity trackerIf a patient has not sent measurements for more than 7 consecutive days

**Figure 6 figure6:**
[figure not shown]
Data integration of the activity tracker, weight scale, and BP monitor in the department’s Cardiology Information System “EPD-Vision”. Company B is the manufacturer of the activity tracker, blood pressure monitor, and weight scale.

### Reasons to Contact Patients

Data will be checked daily by a project-dedicated health care professional. When prespecified irregularities are seen in the data, a patient will be contacted within 48 hours by email or phone. These data irregularities are standardized and shown in Textbox 2.

### Reasons to Adjust Therapeutic Regimen

Data will be discussed by the data reviewer and the patient’s treating physician or nurse practitioner. There are several reasons to contact the patient, which are detailed below.

#### BP Monitor

Warnings generated by the system on the basis of BP measurements will be reviewed by a project-dedicated health care professional. The reason to change medication will be left to the discretion of the treating physician.

#### Single Lead Electrocardiogram

In cases of newly diagnosed arrhythmias lasting at least 30 seconds (eg, atrial fibrillation, atrial flutter, nodal or ventricular escape rhythms, ventricular tachycardias) or at least 4 newly diagnosed asymptomatic premature ventricular contractions, a 24-Hour Holter ECG will be performed. Patients noting chest pain or shortness of breath as symptoms will be contacted for an interview by telephone. The decision to change medication or to refer the patient for invasive therapy will be left to the discretion of the treating physician.

#### Weight

Weight will not be a primary reason to change a therapeutic regimen. Patients can be given lifestyle advice, depending on their height, weight, and estimated fat percentage; this will only be done at scheduled outpatient clinic visits.

#### Activity

Activity tracking data is not a primary reason to change a therapeutic regimen. Patients can be advised to exercise more or less, depending on the data; this will only be done at scheduled outpatient clinic visits.

### Nonadherence

If a patient does not send measurements from any of their four devices for 21 consecutive days, they will be considered nonadherent. A standardized email will be sent to the patient, stating that measurements have not been received and that they are urged to contact the hospital in case of any technical difficulties. If no answer is received within 21 days or no measurements are seen within 21 days, the patient will be called by telephone. Any technical difficulties or objections by the patient will be assessed and solved if possible. After this phone call, if the patient starts sending measurements, they will be considered adherent again. This patient will be sent a standardized email in case they become nonadherent again. If the patient does not start sending measurements, they will not be approached again by email or by telephone to try to affect their nonadherence. However, this patient will not be excluded from the trial, and will still be followed-up according to *The Box* protocol. If patients notify the hospital that they want to have regular outpatient clinic visits, they will be followed-up according to the regular follow-up protocol.

### Questionnaires

All patients, in both the intervention and control groups, will be asked to fill-in a short form health questionnaire (SF-36) [18], a patient satisfaction questionnaire [19], a medication adherence questionnaire, and an International Physical Activity Questionnaire (iPAQ; to assess the patient’s level of physical activity) [20]. These questionnaires will be used within one month after myocardial infarction, six months after myocardial infarction, and twelve months after myocardial infarction.

### Privacy of Study Participants

To anonymize the data, patients will receive an email address consisting of a study code, which they can use to create their Withings and AliveCor accounts. The corresponding names will be kept in a separate, password-protected database.

### Ethical Conduct

The study is approved by the Hospital’s Medical Ethics Committee (P16.070). All procedures will be conducted in accordance with the principles of the Declaration of Helsinki (version 10, October 2013) and in accordance with the Dutch Medical Research Involving Human Subjects Act (WMO) and Good Clinical Practice. Written offline informed consent will be obtained from all participants. The devices used in this study and described above have been approved by our Hospital’s Instrumentation Department. All devices are CE-marked and are available for sale in the European Union. All devices have been purchased by our department for this study. No manufacturer has a role in the study design, data collection, statistical analysis, or writing of the manuscript. No financial support was received for this study from any device manufacturer. All devices are provided to study participants who are randomized to *The Box* group free of charge.

### Study Withdrawal

Patients who are randomized to *The Box* group can be withdrawn from the study if they are either nonadherent (as discussed above) or if they themselves wish to withdraw from the study. Patients who withdraw from regular follow-up are considered lost to follow-up.

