### Statistical Analyses

A power calculation was done using R software [24], which is based on a comparison of two proportions of patients with controlled BP (defined as an SBP of 139 mmHg or less and a DBP of 89 mmHg or less). We hypothesize that in the *The Box* group, 95% of the patients will achieve controlled BP, while in the control group, 75% will achieve controlled BP [25]. For this calculation, an alpha of 0.05, a beta of 0.20, and a margin of 0.07 were chosen, yielding a sample size of 200 patients.

Data will be analyzed according to the intention-to-treat principle. Causes of missing data will be tabulated (Multimedia Appendix 1). The percentage of missing data is expected to be low. Therefore, complete case analyses will be done. Analyses will be based on the missing-at-random assumption. If the percentage of missing values exceeds 7%, multiple imputation will be applied in the analysis of the data.

After finishing the study (defined as the last patient’s last visit), the proportion of patients with controlled BP will be compared with a Chi-square test. Logistic regression might be done if serious imbalances of baseline variables exist, to correct for potential confounding variables. Percentages of patients with controlled BP at three months (secondary outcome 1), and percentages of patients in which a previously unknown sustained arrhythmia is detected, will also be compared with a Chi-square test.

Scores of questionnaires (patient satisfaction questionnaire, MMAS-8 scale, iPAQ questionnaire, and SF-36 questionnaire) and health care utilization will be compared using an independent t-test. Major Adverse Cardiac Events (MACEs) will only be reported. As the study is underpowered, no statistics will be done on MACEs. The numbers will be hypothesis-generating.

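### The withdrawal rule lets nonadherent Box patients be taken out of the study, against the nonadherence rule, and opens a one-arm exclusion after randomisation

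*Protocol article*

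**What the plan says.** All places are in the protocol article.

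- **Nonadherence, definition:** "If a patient does not send measurements from any of their four devices for 21 consecutive days, they will be considered nonadherent". An email follows, then a telephone call.
- **Nonadherence, consequence:** if the patient still sends nothing after the call, the attempts to restore adherence stop. The section then states: "However, this patient will not be excluded from the trial, and will still be followed-up according to" The Box protocol.
- **Study Withdrawal, The Box arm:** patients in that "group can be withdrawn from the study if they are either nonadherent (as discussed above"). The patient's own wish to leave is listed as a separate ground.
- **Study Withdrawal, control arm:** "Patients who withdraw from regular follow-up are considered lost to follow-up". No nonadherence ground is given.
- **Statistical Analyses:** "Data will be analyzed according to the intention-to-treat principle". Then: "The percentage of missing data is expected to be low. Therefore, complete case analyses will be done". Missing-at-random is assumed, and multiple imputation replaces complete-case analysis once missing values exceed 7%.
- **Study Outcomes:** the primary outcome is controlled blood pressure at the 12-month clinic visit.

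**The concern.** The withdrawal section refers back to the nonadherence definition, so both rules cover the same patient: one keeps that patient in the trial, the other lets the patient be removed. Staff cannot follow both.

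The removal option exists in one arm only, because controls receive no devices and cannot meet the definition. It depends on behaviour after randomisation, and it is discretionary, with no criterion for who is withdrawn and who stays. The trial is open, and project staff review the home blood pressure data of The Box patients every day.

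What is at stake is the randomised comparison on the primary outcome. If patients who disengage from the devices have worse blood pressure control than the rest, leaving them out of one arm makes The Box look better than it is.

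**Working it through.** **Step 1. The two rules side by side.** For a Box patient who is still silent after the email and the call, the Nonadherence section requires continued follow-up and the Study Withdrawal section permits withdrawal. The patient's own decision to leave is a separate ground, so it does not explain the nonadherence ground.

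**Step 2. When this reaches the primary analysis.** It does so only if the 12-month clinic reading of a withdrawn patient is not collected or not used. The article does not settle this. If the reading is absent, the default analysis excludes the patient.

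**Step 3. How many patients can be lost before imputation starts.** There are 200 patients randomised 1:1, so 100 per arm.
- If 7% is an overall figure: 0.07 × 200 = 14 patients. All could be in The Box, which is 14% of that arm, and the threshold would not be exceeded.
- If 7% is read per arm: 7 of the 100 Box patients.

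**Step 4. Size of the shift under complete-case analysis.** The control rate of 75% comes from the power calculation and is applied to both arms, so there is no true effect. The share withdrawn from The Box (w) and the proportion of them who would have been controlled (q) are assumptions; the article gives neither.

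Retained Box rate = (0.75 − w·q) / (1 − w)

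| w | q | Calculation | Retained rate | Shift |
|---|---|---|---|---|
| 0.10 | 0.65 | 0.685 / 0.90 | 76.1% | +1.1 points |
| 0.10 | 0.45 | 0.705 / 0.90 | 78.3% | +3.3 points |
| 0.14 | 0.65 | 0.659 / 0.86 | 76.6% | +1.6 points |
| 0.14 | 0.45 | 0.687 / 0.86 | 79.9% | +4.9 points |
| any | 0.75 | 0.75(1 − w) / (1 − w) | 75.0% | 0 |

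The 10% case stays complete-case on the overall reading only while at most 4 controls are also missing (10 + 4 = 14). On the per-arm reading the ceiling is w = 0.07. That gives 0.7045 / 0.93 = 75.8% at q = 0.65 and 0.7185 / 0.93 = 77.3% at q = 0.45, a shift of +0.8 to +2.3 points.

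**Step 5. Effect on the test.** Take the two-sided 5% chi-square test without continuity correction, with 100(1 − w) Box patients against 100 controls. Let d be the shift, SE₀ the pooled and SE₁ the unpooled standard error. The chance of rejecting a true null is

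1 − Φ((1.96·SE₀ − d)/SE₁) + Φ((−1.96·SE₀ − d)/SE₁)

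- w = 0.10, q from 0.65 to 0.45: 5.3% to 8.3%.
- w = 0.14, q from 0.65 to 0.45: 5.7% to about 12%. At q = 0.45, d = 0.0488, SE₀ = 0.0616 and SE₁ = 0.0612.
- q = 0.75: 5%.

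Exact binomial enumeration of the same test gives 5.4% to 8.6% and 5.7% to 12.4%.

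**The case against.** The contradiction itself is hard to dispute. The case on the other side concerns how far its consequences go, and much of that case stands.

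- **Loss of the outcome is inferred.** The article does not say that data collection stops for a withdrawn Box patient; it uses the term lost to follow-up only for those who leave regular follow-up. The 12-month clinic visit is part of usual care, so a reading may exist. A reader might infer that the analysis is bound not to be intention-to-treat. The text supports only the conditional statement, since withdrawal is permitted rather than required and the reading might still be used.
- **Worse control among nonadherent patients is assumed.** It is plausible, because they lose the monitoring meant to improve control, but the article gives no control rate for them.
- **Larger losses leave the complete-case analysis.** A reader might take 20% of The Box withdrawn and obtain +2.5 to +7.5 points, which appears to exceed the 0.07 margin. But 20 of 200 is 10% missing overall, so the plan moves to multiple imputation and the formula no longer describes the planned analysis. The margin is also an input to the power calculation only; the chi-square test described does not use it.
- **Other outcomes.** A reader might extend the bias to every questionnaire outcome. No direction can be shown for these, and some questionnaires may be completed before withdrawal.

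What does not stand is the idea that the 7% rule disposes of the matter. Up to 14 losses, all possibly in one arm, stay complete-case on the overall reading. Above that, imputation removes the bias only if missing-at-random holds, and that is doubtful if withdrawal follows disengagement and the patient's home readings have stopped.

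**Conclusion.** The point holds as a contradiction between the Nonadherence and Study Withdrawal sections that can affect one arm only. Following the withdrawal section would allow a discretionary exclusion after randomisation, which does not fit the stated intention-to-treat principle.

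Bias in the primary outcome is possible, not established. It requires both that the 12-month reading of withdrawn patients is missing or unused and that their control rate differs from that of the rest. With 75% controlled in both arms and withdrawn patients controlled at 45-65%, the spurious gain for The Box is 1.1 to 3.3 points at 10% withdrawn. It is 1.6 to 4.9 points at 14% withdrawn, the most that stays complete-case on the overall reading of the 7% rule. It is zero if withdrawn patients are controlled at 75%. Confidence is high in the contradiction and the one-arm asymmetry; the size and direction of bias are illustrative.

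This should be corrected because it bears on the validity of the primary comparison and costs almost nothing to put right.

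**What to change.** Reconcile the two sections:

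1. Delete nonadherence as a ground for withdrawal in Study Withdrawal, so that it agrees with Nonadherence. State that stopping device use is not leaving the study. The existing sequence of email and call can stay; only persistent silence after the call ends those contacts.
2. Use one study-withdrawal rule for both arms: withdrawal of consent.
3. Seek the 12-month clinic blood pressure and the questionnaires for every randomised patient who has not withdrawn consent, whatever their device use, and analyse all patients as randomised.

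The cost is small: one sentence to delete or amend, and a short statement on outcome collection. No visit is added. The 12-month clinic visit belongs to regular follow-up and is not among those replaced by electronic visits in The Box, where only the first and third are replaced. The 12-month questionnaires are already planned for both arms.

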## Results

### Study Outcomes

The primary outcome of this study is the percentage of patients with normalized BP (defined as SBP <140 mmHg and DBP <90 mmHg), as measured at the 12-month outpatient clinic visit. Secondary outcomes of this study are detailed in Textbox 3.

Secondary outcome measures.The percentage of patients with controlled BP (defined as SBP <140 mmHg and DBP <90 mmHg), as measured at the 3-month outpatient clinic visit.Patient satisfaction, as assessed by the patient satisfaction questionnaire [18].Health care utilization, defined as an outpatient clinic visit, emergency care visit, or admission for any reason. This factor will be measured via questionnaires and verified by EMR data.Major Adverse Cardiac Events (MACEs)a. Death of any causeb. Cardiac deathc. Recurrent STEMId. Recurrent NST-ACSe. Revascularizationf. Hospitalization for heart failureg. Transient Ischemic Attackh. Ischemic strokePropensity of medication adherence, measured by the 8-item Morisky Medication Adherence Scale (MMAS-8) [21].Physical activity, as measured by the iPAQ [20].Quality of life, measured by the SF-36 [19].Percentage of patients in which a previously unknown sustained arrhythmia (>30 seconds) is detected.Cost-effectiveness, expressed as the incremental cost-effectiveness ratio.

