### Economic Analysis

To assess the cost-effectiveness of the intervention, costs per quality adjusted life year (QALY) will be calculated. The analysis will be performed from a societal perspective with a time horizon of one year. Patients will receive a health care resource use questionnaire at 6 months and 12 months. In this questionnaire, a patient will be asked to fill in their total health care utilization, such as outpatient clinic visits, emergency visits, admissions for any reason, and visits to the general practitioner. All outpatient clinic visits, emergency visits, and admissions for any reason reported in the questionnaire will be verified by EMR data. In the same questionnaire, the patient will be asked to fill in total medication use. All health care and medication use will be multiplied with standard cost prices to calculate costs [22]. To calculate indirect costs, patients will be asked to note absence from paid and unpaid work. Productivity costs will be calculated using the friction cost method. Absence will again be multiplied against standard cost prices [22]. QALYs will be calculated from utility scores from the SF-36 questionnaire, which will be administered at baseline, 1 month, 6 months, and 12 months [19,23]. Finally, costs and QALYs in both groups will be compared. It is our hypothesis that societal costs will be lower in the intervention group.

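### The withdrawal rules treat leaving the assigned follow-up as leaving the trial, which fits poorly with intention to treat and conflicts with the Nonadherence section

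*Protocol article*

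**What the plan says.** Two sections of the protocol article govern what happens when a patient departs from the assigned follow-up.

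- **Study Withdrawal.** Box patients "can be withdrawn from the study if they are either nonadherent (as discussed above) or if they themselves wish to withdraw from the study". The next sentence reads: "Patients who withdraw from regular follow-up are considered lost to follow-up". It does not name the control arm.
- **Nonadherence.** For a Box patient who sends no measurements even after the telephone call: "However, this patient will not be excluded from the trial, and will still be followed-up according to" the Box protocol. For a Box patient who prefers the clinic: "If patients notify the hospital that they want to have regular outpatient clinic visits, they will be followed-up according to the regular follow-up protocol".

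Three other places bear on the consequences.

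- **Study Outcomes.** The primary outcome is controlled BP "as measured at the 12-month outpatient clinic visit".
- **Statistical Analyses.** "Data will be analyzed according to the intention-to-treat principle". The analysis is complete case under a missing-at-random assumption, with causes of missing data tabulated. Then: "If the percentage of missing values exceeds 7%, multiple imputation will be applied in the analysis of the data".
- **Economic Analysis.** The stated use of the EMR is verification: "All outpatient clinic visits, emergency visits, and admissions for any reason reported in the questionnaire will be verified by EMR data".

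**The concern.** Regular follow-up is a care track of four clinic visits. A patient can drop that track and still be willing to come once for a BP reading at 12 months, to return a questionnaire, or to have the hospital record read. The Study Withdrawal section does not allow for this: leaving the track is itself classed as loss to follow-up, and a Box patient can be taken out of the study for not sending measurements.

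An intention-to-treat analysis needs outcomes for everyone randomised, whether or not they kept to the assigned care. A rule that turns departure from care into absence of data works against that. Patients who disengage may differ in BP control and in events from those who stay, so the complete cases may no longer represent the randomised arms. Major adverse cardiac events (MACE) are to be reported without statistics, so uneven capture between arms would be hard to recognise in the results.

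The two sections also disagree about the same patient. Study Withdrawal points back to the nonadherence definition and permits removal from the study; Nonadherence says such a patient is not excluded.

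**Working it through.** **The rules side by side**

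| Situation | Nonadherence section | Study Withdrawal section |
|---|---|---|
| Box patient stops measuring | Stays in the trial | Can be withdrawn |
| Box patient asks for clinic visits | Moves to regular follow-up | Not addressed |
| Box patient wishes to leave | Not addressed | Can be withdrawn |
| Any patient leaves regular follow-up | Not addressed | Lost to follow-up |

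The first row is a contradiction. The last two rows equate leaving follow-up with leaving the trial. No row says whether outcomes are still sought.

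**Inputs for an illustration**

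The article has no figure on this point to reproduce: it says only that missing data should be few.

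- From Statistical Analyses: expected controlled BP 95% (Box) and 75% (control), a true difference of 20 points; total 200 patients.
- From Study Design: 1:1 allocation, so 100 per arm.
- Assumed: the share *d* of an arm that is lost and the true controlled rate *q* among those lost.

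**Observed rate among complete cases** = (*p* − *d*·*q*)/(1 − *d*)

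Loss in the control arm only, *p* = 0.75:

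- *d* = 0.05, *q* = 0.60: (0.75 − 0.03)/0.95 = 75.8%; difference 19.2 points.
- *d* = 0.10, *q* = 0.50: (0.75 − 0.05)/0.90 = 77.8%; difference 17.2 points.
- *d* = 0.10, *q* = 0.75: (0.75 − 0.075)/0.90 = 75.0%; difference 20.0 points.
- *d* = 0.10, *q* = 1.00: (0.75 − 0.10)/0.90 = 72.2%; difference 22.8 points.

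Loss in the Box arm only, *p* = 0.95:

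- *d* = 0.10, *q* = 0.75 (assumed): (0.95 − 0.075)/0.90 = 97.2%; difference 22.2 points.

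The sign therefore depends on which arm loses patients and on who they are.

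**Imputation trigger**

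If 10 of 100 controls are lost and no Box patients, overall missingness is 10/200 = 5%. That is below the 7% trigger if it is read over all patients, so the complete-case result stands. Read within the arm, 10% exceeds it.

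**Power**

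For a plain two-sided 5% comparison (the article does not state sidedness), power = Φ[(0.20 − 1.96·SE₀)/SE₁], with SE₀ pooled and SE₁ unpooled.

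- 100 v 100: SE₀ = 0.0505, SE₁ = 0.0485, power 98.1%.
- 100 v 90: SE₀ = 0.0511, SE₁ = 0.0506, power 97.6%.

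Power hardly moves. What is at risk is bias and uncounted events.

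**The case against.** The strongest objection is to a reading that the text invites: that a control patient who leaves is lost while a Box patient who leaves is kept, so the comparison is biased against The Box. The documents do not support this, for three reasons.

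- The fallback in the Nonadherence section is for a Box patient who changes the mode of visit and still attends. The control patient in question stops attending. These are different behaviours.
- Study Withdrawal also lets Box patients be withdrawn, for nonadherence or at their own wish. Nonadherence is a route out that controls do not have, so Box losses could be the larger.
- The sentence on regular follow-up could also cover Box patients who were moved to it.

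A reader might also infer that the hospital record could supply whatever is lost. It cannot supply the primary outcome, which is a clinic BP at 12 months. Its stated role is to verify use that patients report by questionnaire. The article does not name a source for MACE, and does not say that events in the record would be ignored.

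Two further objections have force. Loss to follow-up is a status label and not in itself a breach of intention to treat; multiple imputation and a table of causes are already planned. And a full protocol or consent form, not shown, may deal with data use after withdrawal.

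What survives is the rule as stated. The silence on consent alone would be no finding in a condensed article. But the article goes further: it fixes a consequence for leaving the care track, and it contradicts itself on nonadherent Box patients. Imputation and tabulation deal with missing outcomes afterwards; they do not replace outcomes that could have been collected.

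**Conclusion.** The point holds as a defect in the retention rule. The Study Withdrawal section merges stopping the assigned follow-up with leaving the trial, in both arms, and disagrees with the Nonadherence section. The result is avoidable missing 12-month BP and event data, possibly unequal between arms, which fits poorly with the intention-to-treat analysis.

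The documents do not determine which arm would lose more, the sign of any bias or its size. The 2.8-point shift in the control rate rests wholly on assumed values (10% of controls lost, half of them controlled, no Box losses) and is small beside the hypothesised 20 points. With the same loss and every leaver controlled, it becomes 2.8 points the other way. This does not undermine the trial, but it is worth correcting because the change is cheap and missed outcomes may not be recoverable later.

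**What to change.** Replace the Study Withdrawal wording with one data-collection rule for both arms, and reconcile it with the Nonadherence section:

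1. Stopping the assigned follow-up, or not sending measurements, is not withdrawal from the trial.
2. Unless consent to data use is withdrawn, keep the patient in the randomised arm and still invite the patient to the 12-month BP measurement and the questionnaires.
3. For these patients, check the EMR for vital status, MACE, admissions and emergency visits to month 12.
4. Reserve lost to follow-up for patients whose status at month 12 cannot be established.
5. Show the planned table of causes of missing data by arm.

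The rule concerns data collection only; the form of care such a patient receives is for the trial team to settle. The sample size does not change. The cost is amended wording, a few extra invitations and a few record checks. Two limits remain: events treated at other hospitals may be missed, and the EMR cannot replace the 12-month clinic BP for a patient who declines to attend.
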